## Abstract

**Background:**

To meet the scientific and political call for effective prevention of child and youth mental health problems and associated long-term consequences, we have co-created, tested, and optimized a transdiagnostic preventive parent-training intervention, Supportive parents – coping kids (SPARCK), together with and for the municipal preventive frontline services. The target group of SPARCK is parents of children between 4 and 12 years who display symptoms of anxiety, depression, and/or behavioral problems, that is, indicated prevention. The intervention consists of components from various empirically supported interventions representing different theorical models on parent–child interactions and child behavior and psychopathology (i.e., behavioral management interventions, attachment theory, emotion socialization theory, cognitive-behavioral therapy, and family accommodation intervention). The content and target strategies of SPARCK are tailored to the needs of the families and children, and the manual suggests how the target strategies may be personalized and combined throughout the maximum 12 sessions of the intervention. The aim of this project is to investigate the effectiveness of SPARCK on child symptoms, parenting practices, and parent and child stress hormone levels, in addition to later use of specialized services compared with usual care (UC; eg. active comparison group).

**Methods:**

We describe a randomized controlled effectiveness trial in the frontline services of child welfare, health, school health and school psychological counselling services in 24 Norwegian municipalities. It is a two-armed parallel group randomized controlled effectiveness and superiority trial with 252 families randomly allocated to SPARCK or UC. Assessment of key variables will be conducted at pre-, post-, and six-month follow-up.

**Discussion:**

The current study will contribute with knowledge on potential effects of a preventive transdiagnostic parent-training intervention when compared with UC. Our primary objective is to innovate frontline services with a usable, flexible, and effective intervention for prevention of childhood mental health problems to promote equity in access to care for families and children across a heterogeneous service landscape characterized by variations in available resources, personnel, and end user symptomatology.

**Trial registration:**

ClinicalTrials.gov ID: NTCT05800522

**Supplementary Information:**

The online version contains supplementary material available at 10.1186/s40359-024-01765-y.

## Introduction

Fifteen to 20 percent of Norwegian children aged three to 18 years have experienced mental health-related difficulties, and seven percent exhibit symptoms compatible with a mental health diagnosis [1]. Furthermore, children often have complex problems, and their symptoms often extend beyond a singular mental health domain or diagnosis [2, 3]. In other words, comorbidity within and across symptom domains is common. These children are at risk of negative developmental trajectories, characterized by poor mental and physical well-being, school absenteeism and dropout, reduced quality of life, and social and professional exclusion later in life [4–6]. To prevent negative life-course trajectories, there has been a societal and political emphasis in Norway on prevention and early intervention for vulnerable children and families [7]. However, the quality of frontline services for children and families varies and has been identified as one of the principal challenges for the municipal sector in Norway [8]. In this protocol, we describe a randomized controlled effectiveness study of a transdiagnostic parent training intervention in municipal frontline services to prevent child and youth mental health problems.

Over the past several decades, evidence-based interventions (EBI) have been developed and tested to prevent and treat mental health problems in youth populations [9]. However, the effectiveness of such interventions has remained stagnant or even declined [10, 11], and the extensive development and testing of interventions has not been reflected in the implementation and utilization of such programs [12]. Many children and families in need of effective treatment or preventive help, do not have access to it [13, 14]. One explanation that has been proposed for this lack of effectiveness, is that resource intensive EBIs targeting singular problem domains do not fit the comorbid problems of clients and the complex realities faced by professionals in frontline services [15]. To address this mismatch, transdiagnostic intervention approaches and user-centered design processes have been suggested as potential solutions [9, 12, 16]. Transdiagnostic approaches may consist of intervention components that target one common underlying factor (e.g., emotion regulation difficulties) associated with multiple problems, or multiple components or common therapeutic principles tailored to fit multiple types of problems within the scope of a single intervention [9]. User-centered design approaches emphasizes co-creation between intervention developers and users to promote ecological validity and usability of intervention measures [12]. The objective of the present study is to investigate the effectiveness of a novel, co-created, transdiagnostic preventive intervention, “Supportive parents – coping kids” (SPARCK), consisting of both components targeting common underlying factors and common therapeutic principles.

SPARCK is a transdiagnostic manualized parent training intervention for prevention of child mental health problems designed for implementation in different types of municipal services in Norway. The target group includes families with children displaying elevated symptoms of internalizing mental health problems, i.e. anxiety and depressive symptoms, and/or externalizing mental health problems, i.e. conduct, opposition, and disruptive behavior problem symptoms. The aim of SPARCK is to provide a preventive frontline mental health intervention that is personalized to fit the needs of the client families, as well as service requirements. By reaching a large user group in need of intervention and various municipal services, SPARCK is designed to promote effectiveness and equity in access to care for children and families across municipalities of different sizes and resource availability [17]. Specifically, the transdiagnostic attribute of SPARCK should be particularly relevant for numerous small municipalities in Norway, which often face resource constraints in implementing diverse interventions for various issues.

### Background for the SPARCK content

There are various motivations for developing a parent-based preventive intervention. Most parents spend much time with and are highly involved in the lives of their children. Therefore, they posit a unique position to provide emotional support, promote basic life skills, and make changes in their children`s day to day life – also after an intervention is terminated. Moreover, there is substantial research suggesting that the quality of parent–child interaction is associated with short and long-term outcomes for children’s internalizing [18] and externalizing problems [19]. As such, parents may play a crucial role in preventing and mitigating mental health problems in children [20]. Specifically, a parent-based intervention makes it possible to address modifiable parenting practices that are associated with maintenance of child symptoms and problems. Adding to this, with a parent-based intervention, other potential barriers in child directed interventions can be avoided (e.g., the child is not motivated, the child and/or parent is worried about stigma, avoiding a focus on the child as the problem).

It is well established that harsh and insensitive parenting practices are associated with development and maintenance of externalizing problems [19], which has led to the development of different strands of family-focused interventions for such problems. The first strand is sensitive relationship enhancement, which promotes secure attachment through teaching parents to be sensitive and responsive to the child’s needs, for instance Attachment and Biobehavioural Catch-up (ABC; [21]). Interestingly, research suggests that enhancement of attachment through child-led play is effective not only for decreasing child disruptive behavior [22], but also reducing child depressive symptoms [23]. As such, sensitive relationship enhancement is a good candidate for a parent-based intervention targeting both externalizing and internalizing problems. Second, emotion socialization theory emphasizes how parents may help children with their emotions through emotional coaching [24, 25]. Research suggests that emotion focused interventions are effective for improving child emotional competence [25] and the Tuning Into Kids intervention have been found to prevent and reduce child externalizing behaviors in a Norwegian context [26]. Moreover, the effect on child symptoms has been found to be mediated by pareting practices [27]. Additionally, emotion socialization interventions are also suggested to prevent and reduce internalizing behaviors in children [28, 29]. Third, behavioral management interventions, for example those based on the social interaction learning model (e.g., Generation PMTO; Parent Management Training – Oregon model), are based on the notion that child disruptiveness develops because of parents rewarding negative behaviors rather than positive behaviors [30, 31]. The social interaction learning model highlights how coercive family processes play a crucial role in the development and maintenance of child behavior problems [31]. In such interventions, positive parent–child interactions are promoted by encouraging cooperation, teaching positive behavior, and through consistent and appropriate limit-setting. Behavioral-management interventions are well-established as effective in reducing externalizing probems [32], but research also suggest potential for reducing child internalizing behaviors [33]. However, there is indication that the externalizing parent training programs need to be optimized to better fit the internalizing symptom domains [34]. In sum, these three types of family focused interventions have been found effective in reducing externalizing problems, although through somewhat different pathways. Addtionally, there is research suggesting that the family focused interventions may affect child internalizing behaviors, making each of them suitable for a transdiagnostic intervention.

Attachment- and behavior-based interventions are also suggested to reduce maladaptive and neglectful parenting [32, 35]. Stressful family environments can impact parental and child stress regulation, notably by elevating hypothalamic–pituitary–adrenal (HPA) axis activity, affecting cortisol and DHEA release [36–38]. Dysregulated cortisol levels and suboptimal cortisol-DHEA ratios have been linked to brain development disruption, cognitive issues, and subsequent internalizing and externalizing mental health problems [39, 40]. Some studies suggest that interventions targeting maladaptive parenting improve caregiver-reported stress, atypical child cortisol levels, and child mental health [41, 42]. Yet, meta-analyses of parenting intervention effects on cortisol have revealed limited impact probably due to methodological limitations (e.g., small samples) and potential ineffectiveness in altering parenting processes [43]. Further, a key issue is that daily salivary cortisol measurements, which is often used, can be unreliable indicators of chronic stress due to diurnal and acute stress influences [43]. A relatively new and promising measure of chronic stress is hair samples, as it measures HPA axis activity over a longer period [44] and thus may represent a more robust marker of chronic stress. Using hair samples may yield effects of parenting interventions on stress hormones and child mental health as theoretically assumed. One objective of the present project is to study if SPARCK is effective in affecting stress hormone regulation as indexed by levels of cortisol and DHEA in hair samples.

Finally, recent research proposes parents as change agents in addressing child internalizing symptoms through alternative approaches beyond those designed for externalizing issues [45–48]. Parent-led cognitive behavioral therapy (CBT), in which parents are empowered to implement strategies in their child's daily life, has been found to be effective [45, 49]. Furthermore, a new research area underscores the substantial role of parental accommodation in perpetuating anxiety symptoms [50, 51]. Family accommodation refers to parents’ behaviors to help the child avoid feelings of distress and anxiety. Avoidant and excessive parental support may reinforce children’s problems and contribute to maintenance or worsening of the symptoms. Initially identified in obsessive–compulsive disorder (OCD), family accommodation now extends to anxiety disorders [52]. Despite positive intentions, such parental responses and avoidance behaviors can inadvertently reinforce children's problems. Moreover, it has been suggested that family accommodation is associated with depressive symptoms, for instance by aiding social withdrawal and engaging in unproductive problem discussions [52] and co-rumination, which refers to excessive discussions with the child about his or her thoughts and problems [53].

Summing up, despite support for some parent directed interventions on child internalizing problems the evidence is still inconclusive, and more research is warranted. For example, family accommodation has been proposed as a key component in family-focused interventions for child anxiety problems [51] but is less studied in prevention samples and in relation to child depressive symptoms. In general, support for preventive parenting interventions has been found for some groups of vulnerable children and families. However, the question of effect of parenting interventions for proximal factors like parenting practices and parental stress, and for more distal, yet important factors like child and youth mental health and stress, has still been pointed out as a current major knowledge gap [54].

### Development and optimization of SPARCK

Inspired by design-based research models focusing on intervention content development such as Multiphase Optimization Strategy, IDEAS impact framework and user-centered design process [15, 55, 56], SPARCK was co-created, tested, and optimized in iterative mixed-methods test-cycles with 31 families and 14 frontline practitioners from 2018 to 2023 [17]. Researchers, clinical psychologists, and service practitioners worked together to develop the theoretical basis, components, and Decision support system accompanying intervention strategies (Fig. 2, see methods section for more detailed description). The Social Interaction Learning model, which forms the basis for the theory of change in PMTO, was used as the starting point for the development of SPARCK. Additionally, the program includes empirically supported components based on attachment theory, emotion socialization, cognitive-behavioral therapy (CBT), and family accommodation. As such, SPARCK addresses problems in families with children displaying externalizing, internalizing, and caregiver challenges, by using intervention components collected from different theories to provide a diverse toolkit to personalize content. The dosage in SPARCK is between 3 and 12 individual sessions, with an optional booster session after three months. SPARCK components are tailored to the needs of the families and children guided by the Decision support system, which is inspired by other transdiagnostic approaches, such as MATCH (Modular Approach to Therapy for Children with Anxiety, Depression, Trauma, or Conduct Problems; [57]. Beyond symptomatology and intervention concepts, SPARCK is essentially about helping parents to promote vital coping skills in their children to deal with daily stressful situations, and to promote healthy child development and parent wellbeing.

### Aims and research questions

We will conduct a randomized controlled trial to investigate the effectiveness of SPARCK compared to usual care (UC) in Norwegian frontline services. In Norway, frontline municipal service sectors, such as child welfare, health, school health and school psychological counselling services, are responsible for providing targeted preventive interventions. The primary objective is to examine whether SPARCK is effective in preventing and reducing negative outcomes and promoting positive outcomes for children and parents. It has been pointed out recently [58], that studies on prevention of anxiety should assess actual disorders in a long-term perspective, and we answer this call by including register data on referrals to specialized services and/or contact with child welfare services. We will also conduct a parallel implementation study to examine the relationship between implementation determinants and clinical and implementation outcomes. However, in this study protocol we focus on the effectiveness part of the project. A separate implementation protocol will be written.

Considering the variability in the quality and quantity of the mental health services for children, youths, and families in the frontline services across Norway, in combination with the theoretical and empirical background presented above, our aim has been to develop a flexible and tailored intervention to address heightened, yet subclinical, symptoms of anxiety, depression, and/or externalizing problems among children and youths. Building on our understanding of the significance of engaging with parents, we posit that alterations in child symptoms will, in part, hinge on corresponding changes in parenting practices. We assume that enhancing parenting practices aimed at fostering children's proficiency in essential life skills could exert a positive influence on both healthy child development and parental well-being (see Fig. 2). Consequently, such interventions may serve as a preventive measure against more severe or enduring mental health problems.

We posit several hypotheses to guide the investigation of SPARCK. More specifically, our primary hypothesis is: H1: Children of parents receiving SPARCK will exhibit lower levels of internalizing and/or externalizing symptoms compared to those who receive UC at a) the end of the intervention and b) 6 months post-intervention. Our secondary hypotheses are: H2: Parents in the SPARCK condition will demonstrate better parenting practices, self-efficacy, and less parental stress than parents in the UC condition at a) the end of intervention and b) 6 months post-intervention; and H3: The effect of SPARCK on child symptoms is mediated by changes in parenting practices; H4: Children (≥ 7 years) and parents in the SPARCK condition will report better subjective quality of life than children (≥ 7 years) and parents in the UC condition; H5: Among those who display abnormal blunted or elevated stress hormone levels as indicated by cortisol and DHEA at pre-intervention, children and parents in SPARCK will be more likely to change towards normative levels at post-intervention than those who receive UC; H6: Children in the SPARCK condition will display lower levels of school refusal than children in the UC condition at a) the end of intervention and b) 6 months post-interventions; and H7: Children in the SPARCK condition will be less likely to be referred to child and adolescent outpatient clinics (Norwegian abbreviation: BUP) or have contact with the Child Welfare Services (CWS) in the following two years compared to children in the UC condition.

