### Data collection

In this study we use a combination of web-based questionnaires to be completed by one parent on mobile phones, pen-and-pencil questionnaires to the children for those who are seven years or older, and hair samples from one parent (i.e., the parent who answers the questionnaires) and the child to measure biomarkers of stress (i.e., cortisol and DHEA). The families receive a hair-sample kit with instructions and necessary equipment for cutting the correct amount of hair. The pen-and-pencil questionnaires for the children is distributed together with the hair-sample kits.

Parent reported data (i.e., the web-based questionnaires by one parent) will be gathered at three time points; pre (T1), post (treatment termination, T2), and six months follow-up (six months after post, T3; see Fig. 1). If the UC group receives open-ended treatments or counselling is delayed in either condition, we will gather T2 parent reported data at 25 weeks after T1 (i.e., T2 is gathered 25 weeks after T1 at the latest). Hair samples will be gathered through participant self-sampling from one parent and the child in all families. Both the hair samples and the child report pen-and-pencil questionnaire is gathered in connection with T1 and at T2. They are instructed to send a text message to the NUBU study coordinators when they have posted the hair-samples and the child questionnaire in the mail, upon which they are ready to be randomized. At T2, the hair-sample kit and the child questionnaire are sent out approximately four weeks after the termination of the intervention (or two weeks after week 25). The delay in the data gathering of hair-samples is simply because the hair-samples reflect the retrospective average bio-marker levels across an 8-week period (two-centimeter hair segment samples).

Finally, register data from Statistics Norway for CWS service contacts and from the Norwegian Patient Register for service referrals will be collected. Data will be obtained two years after post-treatment. Parents have consented to collection of register-data up to 5 years after follow-up, but the potential five-year long-term register data collection depends on the project receiving additional funding.

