### Measures

Various measurement instruments are used to investigate the primary hypothesis of parent reported change in child externalizing and internalizing symptoms. and the secondary hypotheses testing various outcomes such as change in proximal family relational outcomes, and other more distal child and parent level outcomes, including moderators, mediators and background factors. An overview of assessment instruments is displayed in Table 1.

**Table 1 Tab1:** Measurement instruments

Measures	Respondent	Level outcome	T1	T2	T3	T4	Weekly assessed
ECBI	Parent	Child	x	x	x		
RCADS-P	Parent	Child	x	x	x		
SDQ-P	Parent	Child	x	x	x		
SRQ	Parent	Child	x	x	x		
Kid-KINDL	Child	Child	x	x^1^			
PAFAS	Parent	Relational	x	x	x		
FRQ	Parent	Relational	x	x	x		
PAB	Parent	Relational	x	x	x		
MaaP-SF	Parent	Parent	x	x	x		
PSS	Parent	Parent	x	x	x		
SWLS	Parent	Parent	x	x	x		
HSCL-10	Parent	Parent	x	x	x		
LES	Parent	Parent	x	x	x		
BioM	Child	Child	x	x^1^			
BioM	Parent	Parent	x	x^1^			
PRQ	Practitioner	Service & Intervention	x	x			
FidQ	Practitioner	Intervention					x
WAI-S	Practitioner	Intervention		x			
WAI-S	Parent	Intervention		x			
UserSQ	Parent	Intervention		x			
RBD	Registers	Child				x	

The parent questionnaires take approximately 20 min to complete. Parents receive 200 NOK (approximately 20 USD) as compensation for the time spent completing the questionnaires and providing hair samples. Instruments with positively formulated items are strategically interspersed among the instruments with negatively formulated items.

For the primary outcome on externalizing problems at T1-3, we will use the parent reported Eyberg Child Behavior Inventory intensity scale (ECBI; [60]) which assesses frequency of children’s externalizing symptoms. For the primary outcomes on internalizing symptoms, we will use the Revised Child Anxiety and Depression Scale parent version (RCADS-P; [61]). In addition, as this is a community level sample with heightened, but not clinical level, symptoms, and may include both children with externalizing and/or internalizing problems, we include the Strengths and Difficulties Questionnaire parent report (SDQ-P). The 20-item total problem scale from the SDQ-P, which assesses multiple correlates of internalizing and externalizing symptoms in children, is included as a primary outcome [62].

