### Data analyses

The effect of the SPARCK vs UC will be indicated through a group (between) by time (within) interaction effect in a mixed effect repeated measures design. Respondents will be included in the analysis if they are assessed at T1 and randomized following the intention-to-treat principle. Missing data at any timepoint will be handled with appropriate missing data techniques depending on the type of data and missing data patterns. For the parent and practitioner-reported web-based questionnaires, completion of all instrument items is mandatory, ensuring that there will be no missing data at the item level. With an expected weak effect size of f = 0.1, GPOWER 3.1 estimates the necessary n to detect group by time interaction with 80% power to be 164, but this is based on no design effects and no dropout. Assuming a therapist intraclass correlation of 0.08 [72], with 4 cases per therapist, the design effect is 1.24, giving an effective n of 80% of the nominal n. Correcting for design effects and dropout the needed effective sample size is 252. Further, a dropout of 20% can be assumed. Forty-nine potential SPARCK practitioners across 24 municipalities have already committed to contribute. With four cases per SPARCK practitioner and four control cases, the total potential N is currently 392. We are thus within reach of a planned 20% safety margin to account for practitioner and participant drop-out.

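### H1 can be met on any of three unranked primary outcomes, but the sample size reproduces as one unadjusted test, so either the 5% error rate or the 80% power per outcome does not hold

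*Protocol article*

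**What the plan says.** In the Protocol article, Aims and research questions, H1 is the only primary hypothesis: "Children of parents receiving SPARCK will exhibit lower levels of internalizing and/or externalizing symptoms compared to those who receive UC". The symptom domains are joined by and/or. The same sentence sets two time points, labelled a) for the close of treatment and b) for half a year later, and joins them by a plain and.

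The Measures section then names three primary outcomes:

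- ECBI intensity: "For the primary outcome on externalizing problems at T1-3, we will use the parent reported Eyberg Child Behavior Inventory intensity scale".
- RCADS-P: "For the primary outcomes on internalizing symptoms, we will use the Revised Child Anxiety and Depression Scale parent version".
- The 20-item SDQ-P total, "which assesses multiple correlates of internalizing and externalizing symptoms in children, is included as a primary outcome".

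None is ranked above the others, and no rule for combining them is given.

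Under Data analyses, the effect "will be indicated through a group (between) by time (within) interaction effect in a mixed effect repeated measures design". Parent-reported data "will be gathered at three time points; pre (T1), post (treatment termination, T2), and six months follow-up". The sample size starts from f = 0.1 and the "necessary n to detect group by time interaction with 80% power to be 164". It is then raised to 252 for a design effect of 1.24 and dropout. Neither alpha nor the correlation between repeated measures is stated.

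**The concern.** The wording of H1 lets success in one domain count as support, and three primary outcomes offer three routes to that success. A sample size worked out for one test belongs to a trial with one route. Both statements are published here and do not fit together, whatever an unseen analysis plan adds. If that plan shares alpha across the outcomes, the 80% power in the article no longer applies to each outcome. If it does not, the chance of a false positive finding for H1 exceeds the nominal level.

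Power per outcome matters in this trial. The Discussion expects a child to change mainly in the symptom domain that he or she presents with, and warns that sample heterogeneity may lead to treatment effects being underestimated. An equal effect of f = 0.1 on all three scales therefore cannot be taken for granted.

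**Working it through.** **Inputs.** From Data analyses: f = 0.1, 80% power, n = 164, therapist ICC 0.08, 4 cases per therapist, dropout 20%, N = 252, potential N = 392. From Data collection: m = 3 assessments. Two arms. Inferred, not stated: alpha = 0.05 and correlation between assessments ρ = 0.5. Assumed: correlations between the three outcomes from 0 to 0.8.

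**1. Reproduce 164.** For the interaction in a repeated-measures design, λ = f²·N·m/(1 − ρ), with m − 1 and (N − 2)(m − 1) degrees of freedom.

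- N = 164: λ = 0.01 × 164 × 3/0.5 = 9.84, df 2 and 324, power 0.805.
- N = 162: power 0.7998. So 164 is the smallest even N that reaches 80%.
- Other settings at alpha 0.05: m = 2, ρ = 0.5 gives 200; m = 3 gives 228, 130 and 98 for ρ = 0.3, 0.6 and 0.7.
- Other alphas at m = 3, ρ = 0.5: 0.10 gives 130; 0.05/3 gives 212.

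Among the settings tried, only m = 3, ρ = 0.5, alpha = 0.05 gives 164. As ρ is not stated, a stricter alpha with an unusual ρ cannot be ruled out by arithmetic alone: at 0.05/3, n is 170 for ρ = 0.6 and 128 for ρ = 0.7. Nothing in the article points to such a choice.

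**2. Reproduce 252.** Design effect = 1 + (4 − 1) × 0.08 = 1.24. Then 164 × 1.24/0.80 = 254.2, within 1% of 252. Backwards, 252 × 0.80/1.24 = 162.6 effective, with power 0.801 at alpha 0.05. No step allows for multiplicity.

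**3. Error rate if any one of three interaction tests supports H1.** Independent outcomes: 1 − 0.95³ = 0.143. Simulation with 400,000 draws:

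| Outcome correlation | Familywise error |
|---|---|
| 0 | 14.3% |
| 0.3 | 13.8% |
| 0.5 | 12.6% |
| 0.7 | 11.1% |
| 0.8 | 10.0% |

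These figures count any significant interaction. The two-degree-of-freedom test has no direction, so the share in SPARCK's favour is smaller.

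**4. Power for one named outcome if alpha is shared (0.05/3 = 0.0167), f = 0.1.**

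| Sample | Effective n | Alpha 0.05 | Alpha 0.0167 |
|---|---|---|---|
| 252 randomised, 20% dropout | 252 × 0.80/1.24 = 162.6 | 0.80 | 0.66 |
| 252 read as analysed | 252/1.24 = 203.2 | 0.89 | 0.78 |
| 392 randomised, 20% dropout | 392 × 0.80/1.24 = 252.9 | 0.95 | 0.88 |

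To regain 80% per outcome at 0.0167, the base n is 212, and 212 × 1.24/0.80 = 328.6, or 329 randomised.

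**5. Power for at least one outcome, f = 0.1 on all three, effective n 164.** For outcome correlations 0.8 to 0, it is 91% to 99% unadjusted and 81% to 97% at 0.0167 each.

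**The case against.** The strongest reply is that a multiplicity rule usually sits in the analysis plan, which is not shown, and that the article never says the tests will be unadjusted. That stands: the absence of a correction is not the point. The point is the mismatch between the wording of H1 and a single-test sample size, which an adjustment elsewhere would not remove, because the published power would then be too high per outcome.

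Two stronger readings are tempting, and the article does not support them.

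- A reader might infer that H1 can be claimed at either time point, making six tests, with an error of 1 − 0.95⁶ = 26.5% if independent and about 25% to 17% for outcome correlations 0 to 0.8 with 0.5 between time points. But H1 joins a) and b) with and, and the planned analysis is one interaction over three assessments. Six tests is an upper reading that applies only if a) and b) are claimed separately. If both time points had to be significant on the same outcome, the error would be only about 2% to 3%.
- A reader might infer that 80% power fails for H1 itself. Under an any-of-three rule it does not, provided f = 0.1 holds on all three outcomes (step 5). The loss is for a single named outcome. The 66% is also the figure at the strictest step: Holm or Hochberg gives at least that much.

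It is also fair to say that the 5% level is inferred from reproducing 164 and is not a statement of the article.

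**Conclusion.** The concern holds in this form: an and/or primary hypothesis and three unranked primary outcomes are paired with a sample size for one unadjusted test. Without a shared alpha, the familywise error for H1 is about 10% to 14%, two to nearly three times the inferred 5%. With alpha split in three, power for a named outcome is about 66% at 252 randomised, not 80%.

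This rests on alpha = 0.05 and ρ = 0.5 (both inferred), on 252 being the number before dropout (the arithmetic indicates so, although the article calls it effective and then mentions dropout again), and on one interaction test per outcome. It should be fixed, but it does not undermine the design: at the potential N of 392, power per outcome after the split is about 88%.

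**What to change.** State alpha and one decision rule for H1 before outcome data are analysed by arm. A direct choice is Holm or Hochberg over the three primary interaction tests at a familywise 5%. One pre-named primary outcome or a defined composite would also do; which of these to prefer is a design choice for the sponsor.

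In the same text:

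- say how the T2 and T3 contrasts support H1a and H1b once the interaction has been tested;
- limit any claim for H1 to the named outcome or outcomes that pass;
- restate power per outcome at the adjusted level, giving the assumed alpha and the correlation between assessments.

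The cost is wording and a less favourable power statement. No extra families are required for the rule itself. If the sponsor wants 80% per outcome at 0.05/3, about 329 randomised would be needed, which lies within the potential 392.
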